## Abstract

Recently, the VALENF instrument, Nursing Assessment by its acronym in Spanish, was developed as a meta-tool composed of only seven items with a more parsimonious approach for nursing assessment in adult hospitalization units. This meta-tool integrates the assessment of functional capacity, the risk of pressure injuries and the risk of falls. The general objective of this project is to validate the VALENF instrument by studying its diagnostic accuracy against the instruments commonly used in nursing to assess functional capacity, the risk of pressure injuries and the risk of falls. An observational, longitudinal, prospective study is presented, with recruitment and random selection based on admissions to six adult hospitalization units of the Hospital Universitario de La Plana. The study population will be made up of patients hospitalized in these units. The inclusion criteria will be patients over 18 years of age with a nursing assessment within the first 24 h of admission and an expected length of stay greater than 48 h and who sign the informed consent form. The exclusion criteria will be transfers from other units or centers. A sample of 521 participants is estimated as necessary. The evaluation test will be the VALENF instrument, and the reference tests will be the Barthel, Braden and Downton indices. Sociodemographic variables related to the care process and results such as functional loss, falls or pressure injuries will be collected. The evolution of functional capacity, the risk of falls and the risk of pressure injuries will be analyzed. The sensitivity, specificity and positive predictive values of the VALENF instrument will be calculated and compared to those of the usual instruments. A survival analysis will be performed for pressure injuries, falls and patients with functional loss. The VALENF instrument is expected to have at least the same diagnostic validity as the original instruments.

**Trial registration** The study will be retrospectively registered (ISRCTN 17699562, 25/07/2023).

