Different studies have shown that nursing assessments do not meet adequate standards of quantity or quality of information [13–15], including studies that have analyzed the completion of information on functional capacity, falls or pressure injuries [12, 16–18]. In fact, these instruments are probably the most commonly used by nurses in adult hospitalization units. These instruments are used independently, but they share constructs, dimensions, and items related to mobility, hygiene, eating, or elimination [19, 20], which implies that their items become redundant and are duplicated [1]. The use of redundant assessment instruments generates skepticism and a perception of wasting time, making it difficult for them to be accepted and implemented in nursing [21]. Therefore, nursing assessments can become an automatic and imprecise task without much input from nurses, affecting not only their validity but also the task of detecting patients at risk [22].

Recently, the “VALoración ENFermera” (VALENF) instrument, Nursing Assessment by its acronym in Spanish, was developed as a meta-tool composed of only 7 items with a more parsimonious approach for nursing assessment in adult hospitalization units [23, 24]. This meta-tool integrates the assessment of functional capacity, the risk of pressure injuries and the risk of falls. Thus, the VALENF instrument has a high predictive capacity on the Barthel (R^2^adj = 0.938), Braden (R^2^adj = 0.926) and Downton (R^2^adj = 0.921) indices, with high interobserver reliability (ICC > 0.9) and good construct validity (RMSEA = 0.0726; TLI = 0.968) and internal consistency (Ω = 0.864), although its sensitivity, specificity, and predictive values for detecting patients at risk of functional loss, pressure injuries, or falls remain to be determined. Consequently, the main objective of this project is to study the diagnostic accuracy of the VALENF instrument compared to instruments commonly used in nursing in adult hospitalization units to assess functional capacity, the risk of pressure injuries, and the risk of falls.

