## Methods/design

### Design

An observational, longitudinal, prospective study with recruitment and random selection of hospitalized patients is presented to estimate the diagnostic accuracy of a meta-tool that collapses other instruments for assessing functional capacity and the risk of pressure injuries and falls in a public hospital in the province of Castellón. The study began in January 2023 and will end in December 2024. Figure 1 presents a general timeline of the study.

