### Data collection

Initially, data collection will take place between October 2023 and May 2024 using Research Electronic Data Capture (REDCap) software. Sociodemographic variables and variables related to the care process will be collected only upon admission. Moreover, the test under evaluation (VALENF instrument) and the reference tests (Barthel Index, Braden Index, and Downton scale) will be employed upon admission, every five days, and upon discharge. Finally, the outcome variables sensitive to nursing care will be collected at the time of discharge.

Nurses who work in the hospitalization units that will participate in the study will carry out the recruitment, data collection and follow-up during the hospitalization of the patients included in the study prospectively.

The recruitment procedure will begin when a patient is admitted to one of the participating hospitalization units, as long as one of the nurses participating in the study is on their work shift during the first 24 h after entry. To randomize the recruitment of the participants, a list of random numbers will be generated for each unit, and a box will be prepared with opaque envelopes with included/not included cards. The nurse who conducts the recruitment will explain the project and request informed consent (IC). The patients will be assessed upon admission, at five days, and upon discharge (Fig. 2).

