### Statistical analysis and diagnostic accuracy

First, a descriptive analysis of the sample will be carried out based on the nature of the variables, and whether there are significant differences in the results of the nursing assessments in terms of the hospitalization units, the type of process (medical or surgical), type of admission (urgent or programmed) and the main diagnosis will be evaluated. For this, the normality and homoscedasticity of the sample will be studied with Shapiro‒Wilk and Levene tests, respectively. Depending on the results, Student’s t test or ANOVA will be applied, depending on the number of groups, or the corresponding nonparametric tests. In addition, an analysis of paired measures will be carried out to analyze the evolution of the scores of the Barthel, Braden and Downton indices, what will serve us as a measure of diagnostic accuracy for our instrument, using these measurements as criteria. Categorical variables will be analyzed using the chi-square or Fisher’s exact test, and correlations will be studied with the Pearson or Spearman test, depending on the application conditions.

After this initial analysis, the cumulative incidence and period incidence of pressure injuries, falls and patients with functional loss will be estimated by unit and overall. A survival analysis will be carried out with pressure injuries, falls or functional loss as dependent variables and the other study variables as independent variables.

Next, the sensitivity, specificity, and positive and negative predictive values of the VALENF instrument will be analyzed to detect patients at risk of pressure injuries, falls, and functional loss using the Barthel, Braden, and Downton indices as reference tests. At this point, it should be considered that the protocolized prevention measures will be applied for those patients who are assessed to be at risk of pressure injury or fall to safeguard the ethical and deontological commitment of nonmaleficence. For this reason, this analysis will be carried out only with the positive cases first and, second, including the true positives with those other patients to whom the corresponding prevention measures were applied. We understand that this situation may bias the diagnostic accuracy results of the VALENF instrument, but we believe that it is a viable solution and that it can also provide information on the effectiveness of the measures used.

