Finally, the VALENF instrument cutoff points will be established to detect the risk of pressure injuries, falls, and functional loss through simple linear regressions with the original instruments and cluster analysis to categorize patients. Moreover, and analysis of the area under the ROC curve will be carried out, considering acceptable values 0.7 to 0.8, excellent if 0.8 to 0.9, and outstanding if more than 0.9, and the Youden index will be used to calculate the optimal cut-off point [31]. A value of *p* < 0.05 will be considered in the comparisons of the hypotheses, and the statistical analysis will be carried out with SPSS v-25 and Jamovi v-2.3.2 software.

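### With Barthel, Braden and Downton as the reference tests, the planned analysis measures agreement with those indices and cannot deliver the promised comparison of diagnostic accuracy

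*Protocol article*

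**What the plan says.** **Promise.** The Abstract states: "The sensitivity, specificity and positive predictive values of the VALENF instrument will be calculated and compared to those of the usual instruments". It adds that VALENF "is expected to have at least the same diagnostic validity as the original instruments".

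**Reference standard.** The Abstract, Variables and instruments, and Data collection all name Barthel, Braden and Downton as the reference tests. Statistical analysis and diagnostic accuracy repeats this: VALENF's sensitivity, specificity and predictive values are analysed "to detect patients at risk of pressure injuries, falls, and functional loss using the Barthel, Braden, and Downton indices as reference tests". No other reference is named for these measures.

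**Relation between the tests.** Design describes VALENF as "a meta-tool that collapses other instruments for assessing functional capacity and the risk of pressure injuries and falls". Background says that "the VALENF instrument has a high predictive capacity on the Barthel" index and the other two, with adjusted R² of 0.938 (Barthel), 0.926 (Braden) and 0.921 (Downton).

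**Observed events.** Falls, pressure injuries and functional loss are recorded at discharge. The statistical section assigns them to incidence estimates and a survival analysis. Straight after naming the indices as reference, however, it notes that at-risk patients will receive preventive measures. It then plans the accuracy analysis first on positive cases and afterwards on true positives together with patients who received prevention, and it accepts that this may bias the results.

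**ROC grading.** The last paragraph of that section grades the AUC, "considering acceptable values 0.7 to 0.8, excellent if 0.8 to 0.9, and outstanding if more than 0.9", without naming the reference for the curve.

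**The concern.** To compare the accuracy of two tests on the same patients, one needs a standard of truth that is neither test. Here the comparator is also the truth. Its own accuracy is then fixed by definition, and nothing is left to estimate on that side of the comparison.

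The headline claim is at stake. A study that shows close agreement between VALENF and three indices it was built to condense could report high sensitivity, specificity and AUC. A reader could take those figures as evidence that VALENF identifies patients who fall or develop a pressure injury as well as the established tools do. Agreement does not show that.

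**Working it through.** **1. The plan's own figure.** Participants and sample gives 521, from a paired comparison of proportions with 95% confidence, 80% (called accuracy there, read here as power) and 10% replacement. The two proportions and the discordance are not stated, so 521 can be neither reproduced nor refuted. Back-solving gives about 469 evaluable patients (469/0.90 = 521.1) or about 473 (473 × 1.10 = 520.3). With the usual McNemar-type formula and independent tests, several unrelated pairs land within two patients of 521; for example, 0.97 vs 0.93 gives 520 and 0.64 vs 0.55 gives 522. The figure does not bear on the point, but a paired comparison of two tests' accuracy would itself need a third standard of truth.

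**2. An index judged against itself.** Let I be the dichotomised index and let it also be the reference.
- Sensitivity of I = P(I+ | I+) = 1.00.
- Specificity of I = P(I− | I−) = 1.00.
- The difference, VALENF minus index, is therefore at most 0. It equals 0 only if VALENF classifies every patient as the index does.

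**3. The prevention caveat beside the reference.** Prevention can change whether a patient later falls or develops an injury. It does not change whether an admission VALENF score agrees with an admission Braden or Downton score. The caveat is coherent if observed events are the truth and has no clear role if the indices are. The section therefore points to two different targets.

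**4. What the reported R² would imply for an AUC against the indices.** Assumptions: bivariate normality, correlation r = √R², and the index dichotomised so that 10%, 30% or 50% of patients are positive. The AUC is the probability that a reference-positive patient has the more adverse VALENF score, from 1,000,000 simulated pairs.

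| R² | 10% | 30% | 50% |
|---|---|---|---|
| 0.921 | 0.986 | 0.977 | 0.975 |
| 0.926 | 0.987 | 0.978 | 0.976 |
| 0.938 | 0.989 | 0.982 | 0.980 |
| 0.70 (check) | 0.935 | 0.909 | 0.903 |

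Sensitivity at a cut-off is less determined. At the matched cut-off and R² of 0.921 to 0.938 it runs from 0.80 to 0.92, with specificity from 0.91 to 0.98.

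**5. Could one score have all three R² values?** If so, two indices must correlate at no less than √(R₁²R₂²) − √((1−R₁²)(1−R₂²)). For Barthel and Braden this is √(0.938 × 0.926) − √(0.062 × 0.074) = 0.932 − 0.068 = 0.864. The other pairs give 0.859 (Barthel, Downton) and 0.847 (Braden, Downton). That is demanding, so the reported R² may come from item-level regressions and the R² of a total score may be lower.

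**6. Precision with observed events as truth.** Expected events are 469 × incidence. The 95% half-width for an assumed sensitivity of 0.80 is 1.96 × √(0.80 × 0.20 / events). The documents give no incidence, so a range is shown.

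| Assumed incidence | Events | Half-width |
|---|---|---|
| 2% | 9 | 0.26 |
| 5% | 23 | 0.16 |
| 10% | 47 | 0.11 |

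**The case against.** The best defence is that agreement with the existing tools is a legitimate aim. The general objective is accuracy measured against those tools, and criterion validity is a coherent goal for a seven-item replacement of three scales. The head-to-head promise rests mainly on the Abstract. This stands, and it is why relabelling resolves much of the problem. It does not rescue the comparative claim, which index-based figures cannot support.

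Four stronger readings are tempting, but the documents do not carry them.
- A reader might infer that VALENF can never match the indices. It can tie, though only with perfect agreement.
- A reader might infer that a top ROC grade is settled before enrolment. The ROC sentence names no reference. Background does not say whether R² belongs to a total score or to a multi-item regression. At R² = 0.70 the modelled AUC is already down to 0.903 at 50% positive, and lower values were not examined.
- A reader might infer that observed events play no part in the accuracy analysis. The prevention text suggests that they might, so the fair statement is that the section is inconsistent.
- A reader might infer that one nurse scores all four tools on each patient. Data collection says only: "Nurses who work in the hospitalization units that will participate in the study will carry out the recruitment, data collection and follow-up". It gives neither the scorer of each tool nor the order of scoring.

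It is also fair to object that an outcome-based comparison has its own weaknesses: few events, outcomes altered by prevention, and possible circularity if functional loss is defined by change in Barthel, which the article does not say. These stand as limits on the remedy.

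**Conclusion.** The concern holds. As written, the index-referenced analysis measures agreement. The usual instruments score 1.00 by construction, so the comparison promised in the Abstract cannot be made and equal-or-better validity cannot be concluded from it. This part needs no distributional assumption. The statistical section is also inconsistent about whether the indices or observed events are the truth.

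The AUC size is conditional. If the ROC analysis uses the indices, if the reported R² carries over to the VALENF score used, and if bivariate normality is adequate, the AUC would be about 0.975 to 0.989, or about 0.90 to 0.94 at R² = 0.70. Under those conditions, a grade in the highest band would say little about predicting falls or pressure injuries.

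**What to change.** - State the reference standard for each accuracy analysis, including the ROC curves, and say to which analysis the prevention-measure steps apply.
- Label index-based sensitivity, specificity, predictive values and AUC as concordance (criterion validity). Do not draw the equal-or-better claim from them.
- Add a paired head-to-head comparison of admission scores against observed events: VALENF vs Braden for pressure injury and VALENF vs Downton for falls. Report differences in AUC (DeLong) and in sensitivity and specificity, with 95% confidence intervals.
- Include VALENF vs Barthel for functional loss only if that outcome is not defined by change in Barthel, or report it with the circularity stated.
- If this comparison is not added, withdraw the comparative claim.

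**Cost.** The change is mainly to analysis wording, because the scores and outcomes are already to be collected. The price is less favourable and less precise results, with half-widths of roughly 0.11 to 0.26 for a sensitivity of 0.80 over the assumed incidences. Prevention will also affect the observed events. Both limits should be reported beside the estimates.

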### Participants and sample

The study population will be made up of patients admitted to the adult hospitalization units of the Hospital Universitario de La Plana. Special service units (intensive care, emergency, operating room and resuscitation), home hospitalization units and maternal-infant and obstetric-gynecological hospitalization units will not be part of the study. Patients over 18 years of age who are assessed in the first 24 h after admission to the hospitalization unit using the Barthel Index, Braden Index, Downton scale and VALENF instrument, are expected to stay longer than 48 h, and who agree to participate in the study and sign the informed consent form will be included in the study. Patients who are transferred from other units of the same hospital and other hospitals will be excluded since their care process is in progress and their assessment on admission does not correspond to the initial assessment after admission.

The sample size was calculated with Epidata v4 and was based on a comparison of proportions for paired data, since the condition of the patient will be unknown at the time of the evaluations, and the reference tests will be used for all subjects. A confidence level of 95%, an accuracy of 80% and a replacement rate of 10% were considered. Thus, the sample size includes 521 participants who will be stratified considering the monthly mean number of discharges from each hospitalization unit (Table 1).

**Table 1 Tab1:** Sample size estimation

Unit	Discharges in 2019	Mean monthly discharges	Estimated n (8 months)
Trauma 1A – A&E	2023	169	115
Gynecological surgery 1B	1303	109	75
Cardiology-Digestion 1D	1751	146	100
Neurology-Pneumology 2A	1550	129	89
Surgery 2B	1397	116	79
Internal Medicine 2D	1101	92	63
**Total sample**	9125	760	521

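### The main accuracy analysis is restricted to undefined positive cases, then to true positives plus patients given prevention, so the promised specificity and predictive values cannot all be validly estimated

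*Protocol article*

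**What the plan says.** In the protocol article, *Statistical analysis and diagnostic accuracy*, "the sensitivity, specificity, and positive and negative predictive values of the VALENF instrument will be analyzed" for risk of pressure injury, falls and functional loss, "using the Barthel, Braden, and Downton indices as reference tests". The section then notes that "the protocolized prevention measures will be applied for those patients who are assessed to be at risk of pressure injury or fall". For that reason "this analysis will be carried out only with the positive cases first and, second, including the true positives with those other patients" who were given prevention.

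The authors concede that the situation may bias the results, call the approach viable, and add that "it can also provide information on the effectiveness of the measures used".

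Three other places bear on this:
- *Participants and sample*: "the reference tests will be used for all subjects".
- *Data collection*: VALENF and the three indices are applied at the same points, namely admission, every five days, and discharge.
- The last paragraph of the analysis section: ROC areas and a Youden cut-off are planned, with no restriction stated.

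**The concern.** Each of the four measures needs particular cells of the 2x2 table. Specificity needs condition-negative patients, and NPV needs test-negative patients, including true negatives. A set limited to positives removes the true negatives, whichever kind of positive is meant. Yet the section announces all four measures for this analysis and defines neither analysis set.

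The second step has a different fault. Prevention is given because a patient was assessed as at risk. If such patients are placed among the true positives, an assessment result becomes part of the definition of the condition it is meant to detect. The output can then look plausible while being partly circular.

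Accuracy is the study's main objective. Followed literally, the rule would give either no usable specificity and NPV, or a PPV and specificity that are too high. The remark on effectiveness invites a further conclusion that the design does not support.

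**Working it through.** **Inputs from the document.** Total sample 521 (*Participants and sample*), and reference tests on all subjects. No accuracy figure is stated, so there is none to reproduce. 521 serves here only as the table total.

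**Assumed inputs.** Condition prevalence 30%, VALENF sensitivity 0.8, specificity 0.7. Rounded to whole patients: TP 125, FP 110, FN 31, TN 255 (sum 521).

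**Formulas.** Se = TP/(TP+FN); Sp = TN/(TN+FP); PPV = TP/(TP+FP); NPV = TN/(TN+FN).

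| Analysis set | TP/FP/FN/TN | Se | Sp | PPV | NPV |
|---|---|---|---|---|---|
| All participants | 125/110/31/255 | 125/156 = 0.801 | 255/365 = 0.699 | 125/235 = 0.532 | 255/286 = 0.892 |
| Step 1, positive = reference- or outcome-positive | 125/0/31/0 | 0.801 | 0/0 | 125/125 = 1 | 0/31 = 0 |
| Step 1, positive = VALENF-positive | 125/110/0/0 | 125/125 = 1 | 0/110 = 0 | 0.532 | 0/0 |
| Step 2, true positives plus prevented FP (as TP), nobody else | 235/0/0/0 | 1 | 0/0 | 1 | 0/0 |
| Step 2, prevented FP as TP, FN kept, no negatives | 235/0/31/0 | 235/266 = 0.883 | 0/0 | 1 | 0/31 = 0 |
| Step 2, prevented patients added but left as FP, FN kept, no negatives | 125/110/31/0 | 0.801 | 0/110 = 0 | 0.532 | 0/31 = 0 |
| Step 2, all FP prevented and recoded, negatives kept | 235/0/31/255 | 0.883 | 255/255 = 1 | 235/235 = 1 | 0.892 |
| Step 2, half of FP prevented and recoded, negatives kept | 180/55/31/255 | 180/211 = 0.853 | 255/310 = 0.823 | 180/235 = 0.766 | 0.892 |

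**Range.** The calculation was repeated for assumed prevalences of 10%, 30% and 50%, each with Se/Sp of 0.9/0.9 and 0.8/0.7.
- All participants: Sp 0.70 to 0.90, PPV 0.23 to 0.90, NPV 0.78 to 0.99.
- Half of FP recoded, negatives kept: Sp 0.82 to 0.95, PPV 0.61 to 0.95, NPV unchanged.
- All FP recoded, negatives kept: Sp and PPV 1.00, NPV unchanged.
- The step 1 pattern is the same in every scenario.

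**Does the stated reason call for the restriction?** Prevention given after an assessment can change whether a fall or pressure injury later occurs. It cannot change a Braden or Downton score taken at the same assessment as VALENF. The reason therefore concerns observed outcomes, while the named references for this analysis are the indices. The analysis section mentions prevention for pressure injury and falls only, yet the restriction is stated for an analysis that also covers functional loss. Since all subjects get the reference tests, the full table in the first row will be available.

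**The case against.** The strongest reply is that the text does not say which instrument triggers prevention. If the usual scales do, VALENF false positives are not all moved. Adding prevented patients then acts like a composite reference: event, or at risk on the usual scale. Take an assumed example of 469 patients with 188 at risk on the scale, 188 VALENF-positive and 169 both. The cells are 169/19/19/262, so specificity is 262/281 = 0.93 and PPV 169/188 = 0.90, neither undefined nor 100%. This stands against any claim of inevitable perfection. But the example keeps the negatives, which the text does not say, and it is then simply the full table against the scale, which is what the fix asks for.

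A reader might infer that specificity, PPV and NPV must all come out undefined or at 100%. The document does not support that. NPV is never forced to 100%: it is undefined, 0% or estimable. PPV remains estimable in step 1 if positive means VALENF-positive. Specificity and PPV reach exactly 100% with negatives kept only if every VALENF false positive received prevention, and coverage is not stated.

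A reader might also infer that the study will yield no specificity at all. The ROC and Youden analyses carry no stated restriction, so that does not follow either.

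Two further points are fair. A condensed article may leave definitions to a fuller protocol, and the authors do admit possible bias. But the restriction is a rule stated in the article, not an omitted detail, and a general bias caveat does not tell the reader that some of the promised measures cannot be estimated.

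**Conclusion.** The concern holds in this form. In step 1, specificity and NPV cannot be validly estimated on either reading of positive cases. With reference- or outcome-positives, specificity is 0/0, PPV 100%, and NPV 0% whenever there are false negatives. With VALENF-positives, sensitivity is 100%, specificity 0% and NPV undefined. These results are algebraic and need no assumption.

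In step 2, counting prevented patients as true positives pushes PPV, and specificity if negatives are kept, towards 100%. How far depends on how many VALENF false positives received prevention, which the document does not allow one to determine. In the 30% scenario, PPV moves from 0.53 to 0.77 (half) or 1.00 (all), and specificity from 0.70 to 0.82 or 1.00. Prevalence, sensitivity, specificity and the share prevented are all assumed.

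The restriction is also unnecessary against the named references. The effectiveness remark is unsupported because prevention follows assessed risk, so treated and untreated patients differ by indication. It would go too far to say that no at-risk patient will be without prevention, since the document does not state coverage. The rule should be changed before analysis because it governs the main objective.

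**What to change.** Rewrite the paragraph in *Statistical analysis and diagnostic accuracy*:

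1. Delete the two-step restriction.
2. For accuracy against Barthel, Braden and Downton, build the full 2x2 table from same-time paired assessments of all participants, and report all four measures from it.
3. For any analysis against observed falls, pressure injuries or functional loss, keep every patient with the observed outcome. Do not recode a prevented non-event as a positive. Show results stratified by recorded prevention as a sensitivity analysis, and state that prevention can bias apparent accuracy.
4. Remove the statement that this analysis informs the effectiveness of the measures, because of confounding by indication.

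The cost is one reworded paragraph and somewhat more analysis. No more patients are needed, and who receives prevention is not affected. The *Discussion* already says that preventive measures will be taken into account in data collection and analysis. The likely downside for the authors is less favourable accuracy figures.

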## Discussion

The limitations of this study mainly involve sample selection bias and measurement bias due to misclassification of the subjects due to the subjectivity of the measurement and underreporting of results sensitive to nursing practice. Another important aspect to highlight is the risk of patient loss during hospitalization follow-up and discharge.

To try to control these limitations, a team of nurses who participate voluntarily in the study and who will receive specific training on the objective and methodology of the study will be selected. Adequate training on REDCap will be carried out, and standardized measurements will be used, verifying compliance with the requirements through a CDRe pilot. In addition, during data collection, the researchers are expected to visit the units periodically to resolve doubts and problems related to the recruitment, data collection, and hospitalization follow-up of participants, and three researchers will audit the REDCap database to verify its accuracy and correct completion and reduce the risk of loss.

Finally, patients at risk (falls or pressure injuries) need preventive measures to avoid these undesirable results. These measures will be applied when necessary and considered in the CDR and data analysis.

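### The two-step accuracy analysis cannot inform on how well the prevention measures work, because assessed risk decides who receives them and no comparator is defined

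*Protocol article*

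**What the plan says.** All references are to the protocol article.

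- *Statistical analysis and diagnostic accuracy* gives the rule for prevention: "the protocolized prevention measures will be applied for those patients who are assessed to be at risk of pressure injury or fall". The *Discussion* repeats the reasoning: "patients at risk (falls or pressure injuries) need preventive measures to avoid these undesirable results".
- The same analysis section handles this in two steps. The accuracy analysis is run first with the positive cases only, and then "including the true positives with those other patients to whom the corresponding prevention measures were applied".
- It admits one consequence: "We understand that this situation may bias the diagnostic accuracy results of the VALENF instrument". It then defends the approach as workable and adds that "it can also provide information on the effectiveness of the measures used".
- The *Design* section describes "An observational, longitudinal, prospective study with recruitment and random selection of hospitalized patients". Chance therefore enters through who is sampled, not through who receives prevention.
- A survival analysis is planned "with pressure injuries, falls or functional loss as dependent variables and the other study variables as independent variables". Prevention is not among the variables listed under *Variables and instruments*. The *Discussion* says only: "These measures will be applied when necessary and considered in the CDR and data analysis".

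**The concern.** To learn whether a preventive measure works, one needs to know what would have happened to similar patients without it. Here the measure is given because the patient is judged to be at risk. Patients with and without prevention therefore differ in the very characteristic that drives falls and pressure injuries. The acknowledged bias covers only the accuracy of VALENF. The remark on effectiveness carries no caveat and is offered as a gain.

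If the clause stands, it could be used to justify either of two unsupported conclusions. Prevention might be credited for every treated patient who stayed free of events, including those whose risk label was wrong. Or prevention might be called ineffective or harmful because treated patients, being at higher risk, had more events.

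**Working it through.** **The plan's own figure.** There is none to reproduce. The clause cites no rate or effect, and the sample size of 521 rests on a comparison of paired proportions, not on any effect of prevention. The article states no event rate, no share of patients at risk and no effect of the measures. All such values below are assumptions.

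**Step 1: is there a comparator?** Prevention goes to patients assessed as at risk. If the rule is followed, at-risk patients without prevention are absent by design. The article describes no random or staggered allocation of the measures and no historical control.

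**Step 2: can the second analysis test effectiveness?** Take a true positive as a flagged patient who had the event. Assume that 30% of the 521 are at risk and treated, 521 × 0.30 = 156.3, with an event risk of 10% without prevention (2% in other patients times a baseline ratio of 5).

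- True ratio 0.5: events 156.3 × 0.10 × 0.5 = 7.8; event-free treated 156.3 − 7.8 = 148.5; pooled 156.3.
- True ratio 1 (no effect): events 156.3 × 0.10 = 15.6; event-free treated 156.3 − 15.6 = 140.7; pooled 156.3.

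The pooled group is the same size whether prevention halves the risk or does nothing. Event-free treated patients are counted as if events had been averted, so the effect is assumed and not estimated. If true positives are instead defined against the reference indices, events do not enter the count at all and the result says even less about effectiveness.

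**Step 3: what would a crude contrast show?** The plan does not specify one, but a reader might reach for it. Let B be the ratio of event risk, without prevention, in at-risk versus other patients. Let T be the true risk ratio for prevention. If exactly the at-risk patients are treated:

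crude risk ratio = B × T

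| Assumed B | T = 0.7 | T = 0.5 | T = 0.3 |
|---|---|---|---|
| 2 | 1.4 | 1.0 | 0.6 |
| 3 | 2.1 | 1.5 | 0.9 |
| 5 | 3.5 | 2.5 | 1.5 |
| 8 | 5.6 | 4.0 | 2.4 |

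Protective measures look harmful only when B exceeds 1/T, that is above 1.43, 2 and 3.33 for T = 0.7, 0.5 and 0.3. Below that, they look protective but weaker than they are. With B = 5 and T = 0.5, the treated risk is 2% × 5 × 0.5 = 5% against 2% in the untreated. Expected events are 156.3 × 0.05 = 7.8 and 364.7 × 0.02 = 7.3, with a crude ratio of 2.5 for measures that halve the risk.

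**Step 4: would adjustment help?** Ordinary regression on the risk score needs treated and untreated patients at the same score. Under the stated rule they lie on opposite sides of the risk threshold, so they do not overlap and the model would extrapolate.

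**The case against.** The strongest reply is that the clause is a modest aside. It says that the approach can provide information, not that it will demonstrate an effect. Effectiveness of prevention is not a study aim, and no hypothesis, endpoint or sample size rests on it. This stands, and it limits the severity. It does not rescue the clause, which still claims evidence that the design cannot give.

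Second, the table in the check describes an analysis that the plan does not contain. That is correct. A reader might infer that the study intends a treated-versus-untreated comparison, but no section specifies one, and prevention is not clearly a covariate in the survival model. The crude ratios show what such a contrast would yield. The planned pooling would err the other way and credit prevention too much.

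Third, a reader might infer that effective measures are bound to look harmful. The documents do not support this. They give no event rates, and the sign depends on the baseline ratio: 2 with a true ratio of 0.3 gives 0.6.

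Fourth, adjustment is not hopeless in every design. Where a known cutoff decides treatment, a regression discontinuity comparison can identify a local effect. The plan proposes none.

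Fifth, the article does not say which instrument triggers prevention, and it speaks of measures given when necessary. Patients on whom the instruments disagree, or who are missed in practice, may be at risk and untreated. That is possible, but the plan neither defines nor uses such patients as a comparator.

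**Conclusion.** The concern holds in limited form. The article attributes to its two-step accuracy analysis a capacity to inform on the effectiveness of prevention that the design does not have. The measures follow from assessed risk, no comparable untreated at-risk group is defined, and the second step presumes the effect in question.

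The size of the distortion cannot be fixed from the document. Over assumed baseline ratios of 2 to 8, a true ratio of 0.5 would appear in a crude contrast as 1.0 to 4.0. This rests on prevention being given to exactly the at-risk patients. The rule covers falls and pressure injuries, so the point does not extend to functional loss.

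Severity is minor. A reader might infer that the study's main conclusions are at risk from this clause. They are not: the aim is the diagnostic accuracy of VALENF, and the separate bias that prevention brings to that aim is already acknowledged in the text.

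**What to change.** In *Statistical analysis and diagnostic accuracy*, delete the closing clause on effectiveness. In its place, state that event rates by prevention status will be reported descriptively only and do not estimate the effect of prevention, because assessed risk determines who receives it.

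The cost is one sentence of protocol wording. Data collection, sample size, the accuracy analyses and patient care are unchanged. The study gives up only a secondary claim that it could not have supported.
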